#### Randomisation

The randomisation process in this RCT will use random permuted blocks to ensure similar numbers of participants in each intervention arm throughout the trial and equal numbers in each arm by the end of the study. Blocks of varying length will be used to reduce the predictability of the allocation sequence. In advance of participant recruitment, an independent researcher will be responsible for generating the allocation sequence using the NQuery statistical software program (version 2.0). (Statistical Solutions, Cork, Ireland; http://www.statistical-solutions-software.com) Sealed envelopes will be used to assign participants to intervention groups. Thus, the allocation sequence will be concealed from all study researchers until the interventions are assigned.

#### Laboratory analysis

All test samples will be analysed at the local hospital laboratory. For those women presenting at GUH, analysis will take place at the GUH laboratory; for those women presenting at MGH, analysis will take place at the MGH Laboratory. Each test sample will have a study-specific label to enable identification. Laboratory samples for plasma glucose were analysed using the hexokinase method (Roche Modular P Analytics Chemistry Systems). GDM will be defined according to the new International Association of Diabetes and Pregnancy Study Groups (IADPSG) criteria [35]. We will apply the cut-off values for a diagnosis of GDM as follows: fasting, 1 hour or 2 hour glucose values of ≥5.1 mmol/l (92 mg/dl), 10 mmol/l (180 mg/dl) or 8.5 mmol/l (153 mg/dl), respectively.

#### GDM diagnosis and treatment, antenatal, delivery and neonatal care

All women with positive test results will be offered GDM treatment. This will involve lifestyle intervention, blood glucose self-monitoring and, if required, insulin. In terms of lifestyle intervention, all women will be offered consultations with a dietician and a diabetes nurse specialist. In terms of blood glucose self-monitoring, all women will be educated and instructed to self-monitor over the remainder of their pregnancy. Women who do not respond to lifestyle intervention after two weeks will be prescribed insulin for the remainder of the pregnancy. Antenatal care for all women with GDM will be provided by specialists in diabetes and obstetrics in secondary care and by the woman’s GP. All deliveries will take place at the local hospital.

#### Data collection

Data collection has two components: baseline characteristic data and clinical outcome data. These are described below.

**Table 1 T1:** Baseline characteristic data

Clinical risk factors	Age
	Ethnicity
	Body mass index
	Parity
	Personal and family history of diabetes
	Smoking status
	Hypertension
	Previous pregnancy ending in perinatal death
	Current medications
	Expected date of delivery
Socioeconomic status	Medical card status^b^
	Private health insurance status
	Employment status
	Education status
	Marital status
	Distance and journey time from hospital and GP settings
	Mode of transport

#### Baseline characteristic data

In order to compare participants in both screening arms, clinical risk factor data and socioeconomic status data will be collected during the recruitment phase, using the baseline characteristic questionnaire (Table 1).

#### Clinical outcome data

Data on a range of clinical outcomes will be collected to explore the clinical effectiveness of the alternative screening programmes. Two sources of data are used:

•Hospital and laboratory database reviews: Data will be extracted from the hospital and laboratory databases on test results, processes of care and pregnancy outcomes.

•Chart searches: Antenatal care documents (combined care cards) will be reviewed at the end of the study to capture processes of care for GDM women, over the course of the pregnancy.

### Outcomes

#### Primary outcome: uptake of screening

The primary outcome in the RCT is uptake of screening in the primary care and secondary care settings. First, the number of screening offers accepted will be assessed by comparing the number of screens offered (via the obstetrics outpatient clinic list) with the number of offers accepted (via the randomisation schedule). Second the uptake rate will be determined by comparing the number of women randomised to each setting to the number of OGTTs performed in that setting (via the GUH and MGH laboratory records).

#### Secondary outcome 1: GDM prevalence

The prevalence of GDM in primary and secondary care settings is a secondary outcome in the RCT. Analysis of the laboratory database will enable the identification of GDM prevalence in both screening groups.

#### Secondary outcome 2: timing of screening

The timing of screening in primary and secondary care settings is a secondary outcome in the RCT. Analysis of the laboratory database will enable a determination of gestational age at the time of screening in both screening groups.

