**Methods/Design:**

This will be an unblinded, two-group, parallel randomised controlled trial (RCT). The target population includes 784 women presenting for their first antenatal visit at 12 to 18 weeks gestation at two hospitals in the west of Ireland: Galway University Hospital and Mayo General Hospital. Participants will be offered universal screening for GDM at 24 to 28 weeks gestation in either primary care (n = 392) or secondary care (n = 392) locations. The primary outcome variable is the uptake rate of screening. Secondary outcomes include indicators of clinical effectiveness of screening at each screening site (primary and secondary) including gestational week at time of screening, time to access antenatal diabetes services for women diagnosed with GDM, and pregnancy and neonatal outcomes for women with GDM. In addition, parallel economic and qualitative evaluations will be conducted. The trial will cover the period from the woman’s first hospital antenatal visit at 12 to 18 weeks gestation, until the completion of the pregnancy.

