In terms of screening, for example, professional groups disagree on whether to recommend universal or selective screening (based on risk factors) [12,18,19]. While some studies have found that universal screening for GDM is superior to risk factor-based screening in terms of number of cases detected, time to diagnosis and treatment, and improved pregnancy outcomes [20,21], others have found no such effects. For example, a review of four trials comparing universal and selective screening, found that there is little high-quality evidence on the effects of screening for GDM on health outcomes for mothers and their babies. The paper concluded that further research is required to see which recommendations for screening practices for GDM are most appropriate [22].

Additionally, the site of screening is likely to be important, both in terms of the location of the screen (regional versus local) and in terms of the provider of the screening service (GP versus hospital). For example The Atlantic DIP study, which offered universal screening to all pregnant women, recorded an uptake rate of only 44% [17]. Follow-up analysis to explain this low screening uptake rate revealed that travel distance to the hospital screening site is an important factor in determining uptake rates [23]. Specifically, the probability of attending for screening is 15% lower for a patient who lives 50 kilometers from a screening centre, compared to an otherwise similar patient who lives closer to the hospital. The corresponding reduction in the probability of attending for an individual residing 100 kilometers away is 30%. This suggests that the availability of GDM screening in local (primary care) settings could result in higher uptake rates; however, this has not been empirically tested to date.

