### Screening in Ireland

In Ireland, although guidelines exist, there is no nationally implemented screening policy for GDM. However, the Atlantic DIP network^a^[1] advocates a universal screening approach for all pregnant women [17]. Part of the rationale for this policy is that research has shown that implementation of selective screening would decrease the number of screens by only 10% while adding significantly to the complexity of the screening process [32]. Currently in Ireland, GDM screening is only offered at secondary care sites. Limiting screening to hospital sites can result in geographical inequalities in access to screening. Additionally, since screening for GDM facilitates the identification of women who are at risk of developing type 2 diabetes in the future and who should undergo long-term health surveillance and preventative measures, women residing in more remote locations are more disadvantaged in terms of both their short- and long-term health.

Thus, it is important to understand if offering a screening programme in primary care would improve uptake rates, access to treatment and pregnancy outcomes. Finding answers to these questions could have important implications for the planning and provision of future GDM screening services nationally. The challenge to the health service is to provide a screening programme that accurately identifies the population at risk and is able to ensure that the uptake rate in the population at risk is on par with international norms for screening programmes. In order to do this, evidence is required on the clinical and cost effectiveness of alternative screening models that could be introduced. A primary versus secondary care based universal screening programme for GDM has not been previously explored or evaluated.

In this paper, we detail an RCT to compare the relative clinical and cost effectiveness of a primary versus secondary care based universal screening programme for GDM. The primary outcome variable is screening uptake rate at each site. Secondary outcomes include gestational age at time of screen, timing of access to antenatal diabetes care services for women with GDM, and pregnancy outcomes for women with GDM. In parallel, we will investigate the cost implications of primary versus secondary care screening. We will also conduct a qualitative analysis of user and stakeholder attitudes, preferences, barriers and facilitators of screening at each site.

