#### Sample size and power calculation

On the basis of a comparison of two proportions a sample of 784 is needed to have 80% power, at the 5% significance level, to detect a ≥10% change in screening uptake. To achieve the required sample size, 1,513 patients will be invited to participate in the RCT, as 74% recruitment and 30% patient attrition (seen in Atlantic DIP) is anticipated. Recruitment will continue until target sample size is reached.

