### Analysis plan

Differences in patient characteristics in primary care versus secondary care will be presented using suitable numerical and graphical summaries. A nonlinear mixed model for a binomial response will be used to compare the proportion of uptake between those in primary and secondary care while adjusting for differences in patient characteristics at baseline as appropriate. The analysis of the secondary responses will involve linear and nonlinear mixed models for continuous and categorical responses and survival models for the analysis of time to event data. The main analysis will follow an intention-to-treat strategy; sensitivity analyses and per protocol analysis will be used to explore the effect of departures from the assumption made in the main analysis. All analyses will be performed using R Statistical advice and analysis will be provided by [name] of the HRB Clinical Research Facility, NUI Galway.

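### Gestational age at screening exists only for women who were screened, so if uptake differs between arms the timing comparison is not protected by randomisation and can be biased in either direction.

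*Protocol article*

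**What the plan says.** The section on secondary outcome 2 names one data source: "Analysis of the laboratory database will enable a determination of gestational age at the time of screening in both screening groups". Table 2 repeats the laboratory database as the assessment method. The abstract lists the outcome among the indicators of clinical effectiveness as "gestational week at time of screening". The section Screening in Ireland words it the same way: "Secondary outcomes include gestational age at time of screen, timing of access to antenatal diabetes care services for women with GDM".

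The primary outcome is whether the test took place: "the uptake rate will be determined by comparing the number of women randomised to each setting to the number of OGTTs performed in that setting". The sample size paragraph states that "a sample of 784 is needed to have 80% power, at the 5% significance level, to detect a ≥10% change in screening uptake", and the abstract allocates women "in either primary care (n = 392) or secondary care (n = 392) locations".

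The Analysis plan makes intention-to-treat the main strategy. For the secondary outcomes it lists mixed models for continuous and categorical responses and "survival models for the analysis of time to event data". It does not say which of these applies to timing of screening, or how a woman who was never screened enters the comparison.

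**The concern.** The variable defined in the protocol has no value for an unscreened woman. Comparing it between arms therefore means comparing two subsets selected after randomisation, and the selecting event is the trial's primary endpoint. If the arms differ in uptake, the higher-uptake arm contains some women whose counterparts in the other arm have no value at all. If those women tend to be tested at a different time from the rest, the arm means differ for that reason alone.

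The Background names timeliness of screening as one way in which the two settings may differ. A spurious delay, or a spurious gain, would be read as a property of the setting when it reflects who attended.

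**Working it through.** **1. The plan's own figure.** The sample size paragraph gives no control rate. The Background cites an earlier regional study that "recorded an uptake rate of only 44"%. Taking 44% v 54%, two-sided 5%, 80% power and no continuity correction:

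n per arm = [1.96 × √(2 × 0.49 × 0.51) + 0.8416 × √(0.44 × 0.56 + 0.54 × 0.46)]² / 0.10² = 391.1, rounded up to 392. The total is 784, which matches the protocol. (45% v 55% also gives 784.)

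**2. Share of extra attenders.** With uptake u0 = 0.44 and u1 = 0.54, women screened only because of their arm make up f = (0.54 − 0.44)/0.54 = 0.185 of the screened women in the higher-uptake arm.

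**3. Assumptions not in the documents.** Women who would attend in either arm are tested uniformly over 24 to 28 weeks, so their mean is 26 and their variance 4²/12 = 1.333 (SD 1.15). The extra attenders are all tested at week m. No woman is tested later because of her arm.

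**4. Formulas.**
- Spurious shift = f × (m − 26).
- Variance in the higher-uptake arm = (1 − f) × 1.333 + f(1 − f)(m − 26)². The second term is the spread between the two kinds of attender and must not be left out.
- Standard error = √(1.333/172.5 + variance/211.7), because 392 × 0.44 = 172.5 and 392 × 0.54 = 211.7.
- Chance of a significant later result = Φ(shift/SE − 1.96).

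**5. Results.**

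| m (weeks) | Shift (weeks) | Shift (days) | SE | Chance of significantly later |
|---|---|---|---|---|
| 26 | 0 | 0 | 0.113 | 2.5% (nominal) |
| 27 | 0.19 | 1.3 | 0.117 | 36% |
| 28 | 0.37 | 2.6 | 0.125 | 84% |
| 30 | 0.74 | 5.2 | 0.156 | over 99% |

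A simulation of 1,000 trials per scenario with 392 women per arm gave 36%, 85% and over 99%. At m = 25 the shift is 0.185 × (25 − 26) = −0.19 weeks: the higher-uptake arm looks earlier, significantly so in about 36% of trials.

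**6. Sensitivity.**
- If the extra attenders have the same spread as the others (variance 1.333 + f(1 − f)(m − 26)²), the shifts are unchanged and the chances at 27, 28 and 30 weeks become about 33%, 81% and over 99%.
- With uptake of 50% v 60% the shift at 27 to 30 weeks is 0.17 to 0.67 weeks; with 70% v 80% it is 0.13 to 0.50 weeks.

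**7. The same scenarios with every randomised woman in the denominator.** The proportion tested by the end of week 28 is 44% v 54% when the extra women are tested at 27 or 28 weeks, and 44% v 44% when they are tested at 30 weeks. In no scenario does the higher-uptake arm look slower. In simulated trials, a Cox model over all randomised women, with the unscreened censored late in pregnancy, gave a hazard ratio for screening of about 1.24 to 1.26 in favour of that arm.

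**The case against.** **The protocol does not state that the analysis set is screened women only.** This is true. It names the data source, makes intention-to-treat the main strategy and lists survival models. A separate analysis plan could treat timing as time to screening in all randomised women, and that would remove the problem. But the outcome as written is a value that only screened women have. Intention-to-treat cannot supply a missing value, and survival models fitted to screened women alone would keep the bias. The outcome worded as a time to an event is secondary outcome 3; gestational age at screening reads as a continuous response. The objection is to the definition, not to missing model detail.

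**Nothing shows that extra attenders are tested later.** This also stands. Under Interventions, appointments in both arms are made for the woman within 24 to 28 weeks. The Background's reason for low hospital uptake is travel distance, not lateness. A reader might infer that primary care will look slower; the documents do not support that. The 30-week scenario lies outside the planned window and is the extreme case.

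**Uptake is reported alongside.** A reader would see the uptake advantage next to the timing result, so the overall conclusion need not be reversed. That limits the harm but does not make the timing comparison valid.

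**A randomised-denominator measure partly restates uptake.** It does, and this is the price of keeping the randomised comparison.

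**Conclusion.** The point holds in conditional form. Secondary outcome 2 is defined only for women selected by the primary outcome, so a difference in uptake removes the protection of randomisation. Bias then follows if the extra attenders differ in timing from the others, and its direction follows theirs. With the 44% v 54% that reproduces the sample size, the spurious shift is 0.185 weeks for each week by which the extra attenders' mean departs from that of the others: 0.19 to 0.74 weeks for 27 to 30 weeks against 26.

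These sizes rest on assumed test weeks and spread. A reader might also infer that about half of the women will be unscreened. That rests on the 44% of an earlier study, not on a control rate stated for this trial. A secondary process outcome is affected; the primary comparison is not.

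**What to change.** Make the randomised comparison of timing the proportion of all randomised women with an OGTT by the end of the planned 24 to 28 week window, with the end of the window defined in advance in completed weeks and days. Optionally add the cumulative incidence of OGTT by gestational week, with every randomised woman in the denominator. Report gestational age among screened women as descriptive only, without a test between arms.

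No new data are needed: OGTT dates come from the laboratory records, and Table 1 lists expected date of delivery at baseline.

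There are two costs. The measure overlaps with the primary outcome and should be presented as such. The Recruitment section also says that outcome data are not gathered from women who discontinue, so the plan must say whether they count as not screened or are censored at discontinuation, with a sensitivity analysis under the other rule.

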#### Secondary outcome 3: time to access antenatal diabetes care for women with GDM

The time to access GDM treatment for positive GDM cases in the primary and secondary care settings is a secondary outcome in the RCT. The Diabetes Clinical Management System (DIAMOND) will be used to collect data on the date of first access to specialist diabetes antenatal care for women diagnosed with GDM. This will enable analysis of time of access to care in both screening groups.

#### Secondary outcome 4: pregnancy outcomes for women with GDM

Pregnancy outcomes for positive GDM cases in the primary and secondary care settings are a secondary outcome in the RCT. The DIAMOND Diabetes Clinical Management System will be used for the collection of data on a range of maternal and neonatal outcomes for women diagnosed with GDM (Table 2).

**Table 2 T2:** Primary and secondary outcomes, and assessment method

**Primary/ secondary**	**Outcome variable**	**Assessment method**
Primary	Uptake of screening	laboratory database
Secondary 1	GDM prevalence	laboratory database
Secondary 2	Timing of screening	laboratory database
Secondary 3	Time to access antenatal diabetes care	Hospital database
Secondary 4	Pregnancy outcomes:	Hospital database
	Maternal outcomes	
	Caesarean section delivery	
	Assisted normal delivery	
	Hypertension	
	Pre-eclampsia texaemia (PET)	
	Antepartum haemorrhage (APH)	
	Post-partum haemorrhage (PPH)	
	Neonatal outcomes:	
	Miscarriage	
	Foetal death intrauterine (FDIU)	
	Stillbirth	
	Admission to neonatal intensive care unit (NICU)	
	Length of stay at NICU	
	Gestational age	
	Size for gestational age	
	Congenital malformations	
	Apgar scores	
	Respiratory distress	
	Hypoglycemia	
	Jaundice	
	Composite perinatal score (neonatal hypoglycemia, respiratory distress, need for phototherapy, birth trauma, 5-minute Apgar score less than 7, or prematurity).	

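### Time to care and pregnancy outcomes are compared between arms among women diagnosed with GDM, a group formed after randomisation by the outcome under test, so they are not randomised comparisons and cannot show whether higher uptake improves pregnancy outcomes

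*Protocol article*

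**What the plan says.** Secondary outcome 4 fixes the population: "Pregnancy outcomes for positive GDM cases in the primary and secondary care settings are a secondary outcome in the RCT". The data come from the diabetes clinical management system, for diagnosed women. Secondary outcome 3, time to access antenatal diabetes care, carries the same restriction.

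The Eligibility criteria exclude women who already have diabetes or a GDM diagnosis. Under Interventions, the oral glucose tolerance test (OGTT) follows randomisation, at 24 to 28 weeks. The primary outcome section sets OGTTs performed against women randomised.

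Four other places bear on the point:

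- Screening in Ireland asks whether primary care screening would raise uptake and also lead to better access to treatment and better pregnancy outcomes.
- The Analysis plan makes intention to treat the main strategy and gives no separate rule for the GDM-only comparisons.
- Secondary outcome 1 says "Analysis of the laboratory database will enable the identification of GDM prevalence in both screening groups" and gives no denominator.
- Clinical outcome data says "Data will be extracted from the hospital and laboratory databases on test results, processes of care and pregnancy outcomes". This sentence is not limited to GDM, but no comparison of pregnancy outcomes in all randomised women is stated. Recruitment adds that women who discontinue contribute no outcome data.

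**The concern.** Membership of the GDM group depends on two events after allocation: attending the OGTT and testing positive. The trial's hypothesis is about attendance. If the arms differ in attendance, the diagnosed women can differ in kind as well as in number. The Background gives a reason to expect this, since it reports that attendance for hospital screening falls with travel distance. Analysing women in their allocated arm does not make two differently selected groups comparable.

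The second difficulty is what the comparison leaves out. Higher uptake could improve pregnancy outcomes by finding and treating cases that would otherwise be missed. Missed cases are outside the comparison in both arms, so a benefit reached by that route would not appear in it. At stake is a selected contrast being read as a randomised estimate of clinical effectiveness.

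**Working it through.** **1. Reproduce the plan's figures.** Sample size and power calculation states that "a sample of 784 is needed to have 80% power, at the 5% significance level, to detect a ≥10% change in screening uptake". It names no base rate. The Background says the earlier programme "recorded an uptake rate of only 44" per cent. Taking 44% v 54%, two-sided 5%, 80% power, pooled variance and no continuity correction:

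n per arm = [1.96 × √(2 × 0.49 × 0.51) + 0.842 × √(0.44 × 0.56 + 0.54 × 0.46)]² / 0.10² = 392 after rounding up, so 784 in total.

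Invitations: 784 / 0.74 / 0.70 = 1,513.5, against 1,513 stated. Both reproduce, so the sample size is not in question.

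**2. Size of the GDM-only comparison.** The Background gives 12.4% prevalence. Assume it holds in both arms and in attenders and non-attenders, and that no GDM is found outside the trial OGTT. GDM pregnancies per arm = 392 × 0.124 = 48.6. Diagnosed = 48.6 × uptake. The 80% v 90% row is an assumed alternative. The half-width uses an assumed 30% event rate: 1.96 × √(0.21/n₁ + 0.21/n₂).

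| Uptake, secondary v primary care | Diagnosed | Undetected, left out | 95% CI half-width |
|---|---|---|---|
| 44% v 54% | 21.4 v 26.2 | 27.2 v 22.4 | 26 points |
| 80% v 90% | 38.9 v 43.7 | 9.7 v 4.9 | 20 points |

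**3. What the comparison would show.** Every risk in this step is assumed. Half the women with GDM have a 40% untreated risk and half 20%. Treatment has a risk ratio of 0.6. Uptake is 44% v 54%. Without selection, diagnosed women have 0.6 × 30% = 18.0% in each arm. All women with GDM have 0.44 × 18% + 0.56 × 30% = 24.7% in secondary care and 0.54 × 18% + 0.46 × 30% = 23.5% in primary care.

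| Extra primary care attenders | Diagnosed women, secondary v primary | All women with GDM, secondary v primary |
|---|---|---|
| Unrelated to risk | 18.0% v 18.0% | 24.7% v 23.5% |
| All high risk | 18.0% v 19.1% | 24.7% v 23.1% |
| All low risk | 18.0% v 16.9% | 24.7% v 23.9% |

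Primary care is truly better in every row. The GDM-only comparison shows no difference, then harm, then benefit, according to who the extra attenders are.

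**4. What the alternatives can deliver.** Cases detected per woman randomised = 0.124 × uptake: 5.5% v 6.7% at 44% v 54% (0.54/0.44, or 23% more cases), and 9.9% v 11.2% at 80% v 90% (0.90/0.80, or 12.5% more). At 44% v 54% the standard error of the difference is √[(0.0546 × 0.9454 + 0.0670 × 0.9330)/392] = 0.0171. Power is Φ(0.0124/0.0171 − 1.96), about 11%.

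For pregnancy outcomes in all randomised women, assume a 30% event risk with untreated GDM and a treatment risk ratio of 0.5 to 0.7. The whole-arm difference is 0.124 × 0.30 × 0.10 × (1 − risk ratio), which is 0.19 down to 0.11 points. With an assumed 10% risk in women without GDM, power at 392 per arm is about 3%, barely above the 2.5% expected by chance in that direction.

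**The case against.** The strongest reply is that women who test positive are worth studying in their own right. The Background names possible differences between settings in timeliness, communication of results and access to treatment for women with a positive test. Those questions concern positive women, and Clinical outcome data says the aim is to explore. This stands as a reason to keep the data, but it does not make the contrast a randomised one.

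Several stronger readings are tempting and should not be drawn:

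- **GDM prevalence has the same defect because it comes from the laboratory database.** A data source does not fix a denominator: uptake uses the same source over women randomised. The prevalence section states no denominator, so this is an ambiguity. Nor would two programmes with equal prevalence among tested women look identical, because uptake is the primary outcome.
- **All clinical effectiveness is judged among women with GDM.** The abstract also lists gestational week at screening, which is measured in screened women. That too is a group formed after randomisation, but it is not restricted to GDM.
- **The 44% v 54% figures are the trial's expected numbers.** The 44% comes from a programme offered to all pregnant women. Here uptake is measured in women who consented by telephone and whose appointments are arranged for them, so it may be higher.
- **An all-women comparison should become the lead analysis.** Step 4 shows that it would have almost no power. It also meets the rule on discontinued women, and the sentence "All deliveries will take place at the local hospital" sits in the section on GDM care, so applying it to every participant is an inference.

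**Conclusion.** The point holds for secondary outcomes 3 and 4. As defined, they compare groups formed by attendance and a positive test, and they omit undetected cases. They cannot answer whether higher uptake improves pregnancy outcomes, which the protocol itself asks. The population and data source are written into the outcome definitions, so this is not a detail left open for an analysis plan.

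The comparison would rest on about 21 v 26 women at 44% v 54% uptake, or 39 v 44 at 80% v 90%. Uncertainty would be about 26 or 20 points either way. These numbers rest on equal prevalence in attenders and non-attenders, no GDM found outside the trial OGTT, and an assumed 30% event rate. The size and direction of any selection bias cannot be derived from the documents; step 3 shows only that either direction is possible. The primary outcome and the sample size are unaffected.

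**What to change.** 1. Replace GDM prevalence as the between-arm secondary outcome with GDM cases detected per woman randomised, counted by allocated arm. Report prevalence among tested women descriptively, with its denominator stated. This needs only the laboratory results and randomisation list already used for the primary outcome, so it costs almost nothing. It is a randomised comparison, but an imprecise one (step 4).
2. Label the GDM-only comparisons of time to care and pregnancy outcomes as descriptive, and state that they are not randomised effects. This changes wording only.
3. Where the hospital databases permit, add a supportive comparison of the Table 2 maternal and neonatal outcomes by allocated arm in all randomised women. Reconcile it with the Recruitment rule that no outcome data are collected from women who discontinue. The cost is data extraction for roughly 700 more deliveries (784 less the 48 to 83 diagnosed in step 2) and possibly a change to the consent wording. The estimate would be free of the selection described here but would have almost no power.
4. Word the clinical effectiveness conclusion accordingly: the trial can test uptake, but it cannot be expected to establish an effect of screening location on pregnancy outcomes.
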